### Data monitoring

This study will be conducted under the supervision of The Joint the Chinese University of Hong Kong–New Territories East Cluster Clinical Research Ethics Review Committee (The Joint CUHK-NTEC CREC). In addition, the Data Monitoring Committee (DMC) has no competing interest in any stages of this study and is completely independent from the sponsor. There will be no interim analysis in this study.

### Participants withdrawal

Participants can withdraw at any time because of personal reasons, adverse events or serious adverse events. An attempt to contact the participant will be made to ask for an explanation for incompliance or termination, and the results of the last assessment should be recorded. For participants who withdraw from the study due to adverse reactions, or treatment failure, appropriate treatment measures should be conducted immediately. Participants are free to withdraw at any time without giving a reason or punishment. All participants are encouraged to attend the follow-up assessment at 24th week for adverse event assessment for the best disease monitoring and participants’ benefit.

### Ethics consideration

This study will be conducted according to the Declaration of Helsinki and International Council for Harmonisation of Technical Requirements for Pharmaceuticals for Human Use (ICH) Guideline for Good Clinical Practice (ICH-GCP). Application for clinical ethical approval will be sought to CUHK-NTEC CREC before the initiation of this study. Participants will be informed that the confidentiality of all information and data will be maintained anonymity. Consent forms should be signed by the participants before the study. All information will be encrypted and only the involved investigators can have access. Password is required to access the data. Participants are free to withdraw at any time without giving a reason or punishment.

### Protocol amendments

In case of protocol modifications, protocol amendments will be submitted CUHK-NTEC CREC for approval (CRE Ref. No. 2022.353).

### Clinical trial insurance

Clinical trial insurance will be purchased according to the University’s policy.

## Discussion

Adolescent idiopathic scoliosis is the most common developmental spine disorder among children. This participant-and-assessor-blinded randomized controlled study allows evaluating the efficacy and safety of an alternative conservative method, the Orthopaedic Manipulation Techniques of the Lin School of Lingnan Region, in the treatment of AIS. Moreover, it helps clarify the effect of OMT-LSLR on the spine and muscle in AIS treatment. If the method does improve the quality of life and reduce the deviations of the spinal curvature in AIS, it can offer an alternative to those patients who cannot or will not opt for surgical treatment. It can also provide a real and meaningful advantage to both the AIS patients and the community.

This study protocol adhered to the Standard Protocol Items: Recommendations for Interventional Trials (SPIRIT) 2013 and SPIRIT-Outcomes 2022 extension [43, 44] in the development and reporting. Being a participant-and-assessor-blinded randomized controlled study, it has several strengths. First of all, quality of evidence is increased by the blinded and randomized study design. Participants and assessors are blinded throughout the study. The blinded design minimizes subjective biases from them. Further, the random allocations sequence preparation is performed by a researcher who are not involved in the participant enrolment, allocation and assessment session. The random allocations sequence generated will be then kept confidential by placing in opaque and sealed envelopes, which minimize the selection bias during the participant recruitment that may affect the outcomes. Second, comprehensive measures are applied to improve adherence from the patients to the study protocol. Standard interventions such as PSSE, and ultrasound assessments are provided for both the manipulation techniques group and the control group. The participants will be closely in touch with the researchers to monitor their symptoms. Nevertheless, participants can receive subsidy in return of following the protocol to complete study. These measures definitely encourage patients to join the study. Third, sham treatment in the control group not only can ensure the blinding but also can increase patient engagement. As the movement of the operator in sham treatment is similar from the real manipulation techniques, sham treatment cannot be easily distinguished by the participants and assessors. Bias can thus be minimized. Additionally, most of the patients would like to have as more interventions as they can. If there is no sham treatment, participant in the control group may think that they have missed some treatment. As a result, they will drop out once they are randomized to control group. Sham treatment can effectively increase the participant compliance as it gives hope to the participants that they still have half chance to receive the manipulation intervention. Forth, 3D ultrasound scanned before and after every manipulation provide a full picture of the change the musculoskeletal situation along the spine. Not only the curvature but also the muscle changes can be monitored to investigate the mechanism of the manipulation techniques.

However, there are some limitations require further comment. First, lack of studies about sham manipulations control groups to verify a standard and unified placebo control group design [45]. Only a few manipulations studies have included a placebo intervention and it is still a challenge for a valid placebo manipulation treatment [46–48]. However, refer to previous study [49], it is generally suggested that the sham manipulations in RCT should be resemble true one in terms of the procedure, treatment frequency and the treatment time to allow similar expectations in the participates from both groups. According to these recommendations, we have designed a set of sham manipulation for OMT-LSLR in AIS treatment with similar movement, except the external force applying on the spine. Further, both treatments will be executed by the same operator to ensure all conditions are as similar as possible. Second, self-compliance for PSSE at home can be an uncertainty which may affect the outcome in the study. Studies demonstrated that PSSE improves health-related quality of life and can halt curve progression or even reduce the Cobb’s angle [50, 51]. The effectiveness of PSSE depends on the compliance of trainings and home exercises [52]. As a result, in order to control the confounding effect, participants need to keep a daily record for their compliance of PSSE throughout the study. Our researchers will keep close contact with the participants and their parents to monitor the compliance of PSSE in both groups.

Based on current studies on conservative treatment of AIS, the quality and quantity of evidence on bracing and PSSE are far ahead of manipulations [53]. The evidence of the effectiveness of OMT conditions remains unproven due to the paucity and low methodological quality of the primary studies [54]. Due to the lack of similar studies for the manipulation in the AIS treatment. This protocol outlines the specific guideline for investigators to study the efficacy and safety of the OMT-LSLR. These guidelines can be applied in other type of manipulation in AIS treatment. It may also help discover the underlying mechanism of manipulation treatment toward the musculoskeletal system. The outcomes have the potential to influence current clinical practice in the conservative treatment in AIS.

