### The assessor and therapist

The participants will be assessed by a registered Chinese Medicine Practitioner with certificate of Scolioscan operation and who is blinded to this study. The manipulation techniques will be performed by a Chinese Medicine Practitioner who is an expert in the Orthopaedic Manipulation Techniques of the Lin School of Lingnan Region with more than 10 years’ experience. The participating subject will receive PSSE training by certified physiotherapists in a physiotherapy centre.

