### The orthopaedic manipulation techniques of the Lin School of Lingnan Region

The Orthopaedic Manipulation Techniques include steps as follow [20]. First, a combination of X-ray examination and palpation will be first conducted to locate the apex of curve before the treatment. Second, the participants will be seated on the treatment chair, with both hands placed behind the neck. The operator will stand at the side of concave curvature, with one arm placed anteriorly to the participant’s neck and the hand holding firm on the participant’s shoulder of the opposite side, while the other hand is fixed at the mid-lower section of the apex of curve. The assistant will firmly anchor the lower limbs. Third, the participant will be requested to bend forward, with the apex of the curve as the pivot point of the spine curvature. After that, forces will be applied using the hand that was placed on the opposite shoulder. This in turn allows the participant’s spine to rotate along with the force applied. Until a resistance is encountered during the rotation, an explosive force will be applied to the spine using the hand. If the participant has double scoliotic curve, the treatment will be implemented first on the inferior site then superior, following the steps as described above.

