### Sham manipulation techniques

For sham manipulation techniques, participants will be instructed to sit on a treatment chair after palpation. The operator will stand at the side of concave curvature, with an arm placed anteriorly to the participant’s neck and the hand holding firm on the participant’s shoulder of the opposite side, while the other hand is fixed at the mid-lower section of the apex of curve. The assistant will firmly anchor the lower limbs. However, the participant only need to rotate slowly without an external force applied to the spine. After that, the operator will stand on the other side and repeat the movement. These non-therapeutic manipulations were performed outside the spinal column with adequate joint slack and without soft tissue pre-tension so that any therapeutic force would not apply to the spine. Rotations to both sides are applied to ensure a broad non-specific movement, which would not produce any therapeutic effect.

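### The stated basis for blinding, that sham resembles real manipulation in all but external force, is not supported by the article's own descriptions of the two procedures; the main exposure is the self-reported SRS-22.

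*Protocol article*

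**What the plan says.** The Discussion of the protocol article lists the sham control as a strength. It reasons that the operator's movement is similar in both arms, so "sham treatment cannot be easily distinguished by the participants and assessors", and concludes that bias is minimised. Its limitations paragraph says that the sham was designed "with similar movement, except the external force applying on the spine", and concedes that a valid placebo manipulation remains a challenge.

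The section on the Lin School techniques describes the real procedure: "the participant will be requested to bend forward, with the apex of the curve as the pivot point of the spine curvature"; the operator then rotates the spine, and "Until a resistance is encountered during the rotation, an explosive force will be applied to the spine using the hand". The section on sham manipulation keeps the seated position, the operator's starting side, the hand placement and the anchoring of the lower limbs. It then departs: "However, the participant only need to rotate slowly without an external force applied to the spine". The operator next moves to the other side and repeats the movement.

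On the assessor, the article says that participants are "assessed by a registered Chinese Medicine Practitioner with certificate of Scolioscan operation and who is blinded to this study". Randomization and blinding adds coded group names, sealed envelopes and a ban on unblinding assessor or participants. Outcomes makes SRS-22 change at week 16 primary and imaging secondary. Ultrasound is done before and after every manipulation.

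**The concern.** The article does not simply declare participants and assessors blinded. It gives a reason, similarity of movement, and says that force is the one exception. If the procedures differ in posture, speed, thrust and number of sides as well, that reason fails on the article's own account.

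This matters most for the primary outcome. SRS-22 is completed by the participant and includes pain, self-image and satisfaction with treatment, all of which expectation can shift. The Discussion says that the sham keeps participants hoping for a half chance of the real intervention, so they know that a sham exists. A participant who feels a thrust, or who is only turned slowly to both sides, has a clue to allocation. Each participant experiences one procedure only, which weakens the clue without removing it.

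A second, conditional exposure is the ultrasound. The assessor's scans bracket each session, and the article presents imaging as the objective counterpart to the questionnaires. The secondary objective concerns change before and after each treatment, so knowing which scan came first could affect that analysis even if the arm stays hidden.

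**Working it through.** **1. The two descriptions side by side.**

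| Feature | Real technique | Sham technique |
|---|---|---|
| Seated, operator starts on concave side, same hand placement, assistant anchors legs | yes | yes |
| Forward bend about the apex | described | not described |
| Rotation | by the operator, until resistance | slow, no external force |
| Thrust | "an explosive force will be applied to the spine using the hand" | none: "the participant only need to rotate slowly without an external force applied to the spine" |
| Sides | concave side; double curves inferior then superior | repeated from the other side for every participant |

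The rotation and thrust rows contain the force difference that the Discussion admits, but also a difference in speed. The forward bend and the two-sided repeat are further differences that it does not mention. For a double curve, the real technique may also bring the operator to the opposite side, so the two-sided repeat is a weaker clue there.

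**2. The plan's own figure.** Sample size estimation gives a difference of 0.4, SD 0.45, 80% power and significance level 0.05; Statistical analysis makes tests two-sided. The two-sample t-test needs 20.87 per group, so 21, as stated. The SD of 0.45 is used in step 3.

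**3. What a bias in SRS-22 would do (assumed sizes; none is in the document).** Let b be a systematic between-group bias in SD units with no true effect, and n the number per arm. The noncentrality is b × √(n/2), and the false-positive rate is the two-sided rejection probability of the t-test with 2n − 2 degrees of freedom. n = 25 is full recruitment; n = 20 is 25 × 0.80 after the planned 20% dropout.

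| b (SD) | SRS-22 points (b × 0.45) | n = 20 | n = 25 |
|---|---|---|---|
| 0.2 | 0.09 | 9.5% | 10.7% |
| 0.3 | 0.135 | 15.2% | 18.0% |
| 0.5 | 0.225 | 33.8% | 41.0% |

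Even the largest of these is below the 0.4 points that the trial is sized to detect.

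**4. What a reader lean in Cobb's angle would do (assumed, and only if the reader knew the arm).** The document gives no SD for Cobb change, so a range is shown. With 25 per arm, SE = SD × √(2/25), and the false-positive rate is P(|Z + lean/SE| > 1.96).

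| Assumed SD (degrees) | SE | 1-degree lean |
|---|---|---|
| 3 | 0.849 | 22% |
| 5 | 1.414 | 11% |
| 8 | 2.263 | 7% |

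**5. Number of scans.** 50 participants × 12 sessions × 2 = 1,200 if every session is completed.

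**The case against.** The strongest reply has four parts.

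- *The assessor is protected in other ways.* The article declares the assessor blinded, codes the group names and forbids unblinding. It does not place the assessor in the treatment room. Scanning around a session shows that a session took place, not which kind. This stands. A reader might infer that the imaging outcomes are biased, or that the assessor can tell the arms apart. The document does not support that: it would need an assessor who sees or hears about a session. Nor is the X-ray reader named, and the degree of manual judgement in the measurements is not stated.
- *An article may leave details out.* Room separation and instructions not to discuss sessions may be in the full protocol. This also stands, and their absence is not counted here. The point rests on what the article states, namely a similarity claim that its own procedures do not bear out.
- *Knowledge of scan order cancels between arms.* This is true for the group comparison if the arm stays hidden. It does not hold for the secondary objective on change before and after each treatment, where no such cancellation occurs.
- *The wording is modest.* The article says not easily distinguished, and similar rather than identical; it also concedes the difficulty of a valid sham, and a participant cannot compare procedures. All fair. But the claim is still used to conclude that bias is minimised, and the stated single exception is incomplete.

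**Conclusion.** The point holds as a contradiction within the article. The Discussion names external force as the only difference and rests indistinguishability on that; the intervention sections also describe a forward bend for the real technique only, a different speed of rotation, and a sham repeated from the other side. Similarity of movement therefore cannot be taken as established grounds for blinding.

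The main exposure is SRS-22 at week 16. Unmasking is not shown to occur; the document gives participants clues without a check on whether they use them. The sizes in the working are illustrations on assumed biases: about 9% to 18% false positives for a bias of 0.2 to 0.3 SD in SRS-22, and 7% to 22% for a 1-degree lean in Cobb's angle over assumed SDs of 8 down to 3 degrees. The Cobb figures further assume that the reader knows the arm. For ultrasound that is a plausible risk only; for the X-ray it is not shown.

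**What to change.** 1. Reconcile the limitations paragraph of the Discussion with the two intervention sections, so that all of them give the same list of differences. Which description of either technique is right is for the investigators; nothing here prescribes one.
2. Qualify the Discussion's claim that the sham is not easily distinguished, presenting it as an intention to be checked.
3. Add one allocation-guess question for participants at week 16, after SRS-22 is completed and before any disclosure, and report the answers by arm beside the primary result.
4. Have the existing assessor measure stored scans under a random code, with arm, session number and before/after label hidden. If the full protocol already provides for this, a sentence in the article is enough.

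Cost: one extra question, file handling for up to 1,200 scans, and readings that are not available at the visit. No added imaging or visits, and the sample size is unchanged.

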## Data Availability

The datasets used and/or analysed during the current study are available from the corresponding author on reasonable request.

## Abbreviations

3D: Three-dimensional
AIS: Adolescent idiopathic scoliosis
ANCOVA: Analysis of covariance
CM: Chinese medicine
CREC: Clinical Research Ethics Review Committee
CUHK-CMSCTRC: The Chinese University of Hong Kong Chinese Medicine Specialty Clinic cum Clinical Teaching and Research Centre
DCM: Data Monitoring Committee
ICH-GCP: International Council on Harmonisation of Technical Requirements for Registration of Pharmaceuticals for Human Use- Good clinical practice
ISYQOL: Italian Spine Youth Quality of Life
OMT-LSLR: Orthopaedic Manipulation Techniques of the Lin School of Lingnan Region
PSSE: Physiotherapy scoliosis-specific exercises
RCT: Randomized controlled trial
SPIRIT: Standard Protocol Items: Recommendations for Interventional Trials
SRS: Scoliosis Research Society
SRS-22: Scoliosis Research Society-22
LSLR: The Lin School of Lingnan Region
TC-SAQ: Traditional Chinese version of Spinal Appearance Questionnaire
